#### Recruitment process and fieldwork

Clinicians working in the participating centers determine whether their patients meet the inclusion criteria described above and invite those patients to be part of the study. Those who accept to participate and complete informed consent procedures are registered using computer software designed for the ACT-ATAC project, including personal identifiers (i.e., name, surname), psychiatric diagnoses, comorbidities, and location data (contact telephone numbers, responsible clinician, clinician's telephone number, etc.). To facilitate the recruitment process, a protocol has been created in the software. After the participant’s data is introduced into the software, he/she is contacted in the first 48–72 h by a research nurse who conducts an extensive interview (see below). The study nurse is independent to any SUD participating center and was recruited exclusively to conduct this interviews. The study procedures are aimed at following up on the tobacco consumption of patients and other variables. The research nurse also informs the patient when he/she will be contacted for follow-up interviews by telephone (at 7 days and 3, 6, and 12 months; Fig. 2).

**Fig. 2 Fig2:**
[figure not shown]
Fieldwork diagram

#### Fieldwork and strategies implemented to overcome the barriers due to the COVID-19 pandemic

The longitudinal fieldwork kicked-off in November 2019 (month 11). The first step of the fieldwork was recruiting SUD centers and working clinicians willing to participate in the project. The pilot study was conducted between November 2019 and February 2020 and allowed us to test the recruitment process and software designed to collect and store data, as well as ensure the correct follow-up of participants. Nevertheless, in March 2020, the COVID-19 pandemic in Spain forced us to modify the follow-up interviews from face-to-face to telephone-based to limit the social contact of the research nurse with the participants. In addition, the rhythm of patient inclusion in the study slowed down from 1 or 2 per week before the lockdown (from March to June 2020) to 2 or 3 per month. Despite this, the study was able to be continue because the SUD centers in Catalonia remained open, though many of the visits were conducted online. Thus, the collaborating clinicians were still able to recruit patients who met the inclusion criteria during the pandemic; however, we recommended that they did so during in-person meetings to better assess participants’ cognitive status and make getting their informed consent easier. These adjustments were possible thanks to the collaboration between the study coordinators, the collaborating clinicians, and the Direction of the Substance Abuse Program at the Public Health Agency in Catalonia, that prioritized our project and contacted clinicians to keep this study on track despite the contextual circumstances. To increase the engagement of clinicians (clinical psychologists, psychiatrists, and nurses), we have conducted monthly online meetings with them to exchange experiences and difficulties in the recruitment process and given them a certificate of participation in the study signed by the Director of the Substance Abuse Program at the Public Health Agency in Catalonia and the Principal Investigator. These meetings are an informal 30-min coffee break in which investigators and clinicians get together and share their experiences regarding the recruitment process and present the latest information on the participants’ profile. A mug with the main inclusion and exclusion criteria has been designed and gifted to clinicians for them to pick up during these meetings (Fig. 3).

**Fig. 3 Fig3:**
[figure not shown]
Clinician’s mug with the inclusion and exclusion criteria

Moreover, to improve participants’ fidelity in the follow-up study, halfway through the study, we started offering 20 euros gift cards to those who answer all of the phone calls during the 12-month follow-up. At the time of submitting this manuscript, 98 patients have been recruited. Thus, we will continue the study until we recruit at least 200 to 250 participants (expected by the end of 2022).

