**Methods:**

Mixed methods project with three substudies. Substudy 1 (S1) comprises heterogeneous discussion groups among clinicians. S2 has two prospective cohorts composed of smokers under treatment for alcohol and/or cannabis use disorder and the clinicians in charge of these patients. Participating smokers will be followed for 12 months and interviewed about their substance use and the tobacco cessation services received using the Spanish version of the users’ Knowledge, Attitudes, and Services (S-KAS) scale. The clinicians will be asked about their self-reported practices in smoking cessation using the Knowledge, Attitudes, and Practices (S-KAP) scale. S3 comprises heterogeneous discussion groups with smokers. Data will be triangulated using qualitative and quantitative analyses. To facilitate the recruitment process, the researchers have introduced several strategies (design clear protocols, set monthly online meetings, extend the project, provide gift cards, etc.).

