**Discussion:**

The results of S1 were used to develop the questionnaires. S2 required some adjustments due to the COVID-19 pandemic, particularly the follow-up interviews being conducted by phone instead of face-to-face, and the recruitment rhythm was lower than expected. Recruitment will last until reaching at least 200–250 users. The fieldwork could not have been possible without the collaboration of the ACT-ATAC team and the introduction of several strategies.

***Trial registration*** The ACT-ATAC project has been successfully registered at Clinicaltrials.gov [NCT04841655].

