## Methods

### Design

We designed a mixed method observational study (Fig. 1). The ACT-ATAC project began in January 2019 and was conceived as a 36-month study. However, due to the COVID-19 pandemic, we have extended the study for eight more months. At the present time, December 2021, we are in month 35 (Fig. 1) and we foresee the study lasting until the end of June 2023.

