### Procedures and statistical analysis

Sessions were recorded and transcribed, preserving participant anonymity and confidentiality, to conduct a thematic categorical content analysis (AC-CT). Thematic axes were proposed to finish constructing the questionnaire needed in the second phase of the study.

S2 (months 11–40): Longitudinal prospective study with smokers in treatment for alcohol and/or cannabis and the clinicians involved (corresponding to November 2019–December 2022; study piloted before the outbreak of COVID-19 in Spain but carried out during and after the severe lockdown of March 2020-June 2020, and currently ongoing).

The second substudy covers aims 2 and 3 and consists of two prospective cohorts composed of (1) smokers in treatment for alcohol and/or cannabis who visited one of the participating SUD programs, who agreed to participate in this study, and had at least one responsible healthcare professional to recruit participants during the first and second year of the study, and (2) the clinicians in charge of these patients.

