#### Variables

Dependent variables include tobacco use, cannabis use, and alcohol use. Tobacco use is rated yes/no. If answering “yes”, we ask the about the tobacco consumption pattern, including nicotine dependence using the 6-item Fagerstrom test [35], and the type of tobacco or other products consumed (i.e., cigarettes, roll-your-own tobacco, combination of both, cigars, e-cigarettes, iQOS); smoking history, including the age when the participant starting smoking, maximum abstinence time, previous quit attempts, and resources used (i.e., none, self-help, professional support, pharmacological treatment, etc.); motivation to quit smoking, measured by a Likert scale from 0 to 10; and willingness to quit smoking, assessed by a 4-item questionnaire that, according to Prochaska and DiClemente’s model, classifies smokers into five stages: pre-contemplative, contemplative, preparation, action, and maintenance [36].

Cannabis use is rated yes/no. If “yes”, we recorded users pattern of consumption, problematic use (yes/no) [37], withdrawal symptoms identified using the Marijuana Craving Questionnaire [38] and reasons for use [39]. Alcohol use is rated yes/no and described according to the variables of consumption included in the Alcohol Use Disorders Identification Test (AUDIT) [40, 41]. A fourth dependent variable is participants’ self-reported smoking knowledge, attitude, and services (S-KAS) received during their treatment in SUD programs [42].

The primary outcome is abstinence from smoking (yes/no), which is self-reported and verified by the exhaled CO concentration only if they report to be abstinent. Self-reported abstinence is defined as “no smoking in the 7 days prior to the assessment point.” Seven-day abstinence was chosen as the consumption measure based on the consensus recommendation in practice guidelines for the assessment of abstinence in patients who are not motivated to quit smoking and who may remain abstinent during various periods of the study [43]. Number of quit attempts in the last year of  > 24-h duration [44] were also recorded. All dependent variables are assessed at baseline and 3, 6, and 12 months of follow-up (Table 1).

**Table 1 Tab1:** Study variables and collection time points (at baseline and follow-up)

Variables	Follow-up							
	Baseline	1 week	3 months		6 months		12 months	
			Abstinent	Not abstinent	Abstinent	Not abstinent	Abstinent	Not abstinent

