## Statistical analysis

After finishing the recruitment and follow-up, abstinence and quit attempt incidence rates will be calculated at baseline and at 3, 6, and 12 months according to whether participants have received any type of smoking cessation intervention. We will also calculate the corresponding risk ratios with 95% confidence intervals (CIs) for quitting and quit attempts.

We will assess the association between receiving smoking cessation support and the two primary outcomes (abstinence and quit attempts) using a Poisson regression model with robust variance for several independent variables (the substance of treatment, sex, types of cessation support [e.g., tobacco-related counselling and medication, etc.]), resulting in RRs with their 95% CIs as their estimators. For analysis, we will use SPSS for Windows version 21 with significance set at p  < 0.05.

We will also conduct exploratory factor analysis for testing the psychometric properties of the S-KAS and S-KAP scales.

S3 (months 40–44): Phenomenological study with discussion groups directed towards patients (will be conducted between December 2022 and June 2023).

This qualitative phenomenological study with discussion groups will use a semi-structured script to answer aim 4.

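### Recruitment forecast to the end of 2022 leaves no room for 12-month follow-up before the stated end of S2 (December 2022) or of the study (June 2023)

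*Protocol article*

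**What the plan says.** - **Recruitment.** The fieldwork section (text below Fig. 3) reports "At the time of submitting this manuscript, 98 patients have been recruited" and continues "we will continue the study until we recruit at least 200 to 250 participants (expected by the end of 2022"). The abstract ties duration to the same target: "Recruitment will last until reaching at least 200–250 users".
- **Follow-up.** The abstract says "Participating smokers will be followed for 12 months". The Variables section for the smokers' cohort says "All dependent variables are assessed at baseline and 3, 6, and 12 months of follow-up". The Statistical analysis section plans abstinence and quit-attempt rates at the same points, including 12 months.
- **S2 window.** Procedures and statistical analysis labels S2 as months 11 to 40, "corresponding to November 2019–December 2022".
- **S3 window.** Statistical analysis gives "S3 (months 40–44") and dates S3 from December 2022 to June 2023.
- **Study end.** The Design section says "we foresee the study lasting until the end of June 2023".

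The article does not date any S2 follow-up beyond these limits, give late entrants a shorter follow-up, or close entry earlier for the 12-month analysis.

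**The concern.** Each date is plausible alone, but together they do not fit. Enrolment to December 2022 plus 12 months runs to December 2023, which is 12 months after the stated end of S2 and 6 months after the stated end of the study.

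The 12-month assessment matters. Aim 2 describes change from the start of treatment to 12 months, Limitations and strengths presents the one-year follow-up as a merit, and the smokers' cohort excludes people who cannot guarantee 12 months. If data collection stops on the stated dates, a sizeable part of the cohort has no 12-month value because of the calendar, in addition to ordinary loss to follow-up. This comes after the recruitment goal has already fallen from the 366 in Sampling method to 200 to 250.

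**Working it through.** **1. Month labels.** With January 2019 as month 1 (Design), month number = 12 × (year − 2019) + calendar month.
- November 2019 = 11, which agrees with the article.
- December 2021 = 36; the article says 35.
- December 2022 = 48 and June 2023 = 54. The article labels the S2 end as month 40 and the S3 end as month 44, which would be April and August 2022.
- The extension is eight months in Design (36 + 8 = 44) and another year in Discussion, while June 2023 is 54 − 36 = 18 months beyond month 36.

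The calendar dates are used below. Taking the month labels literally would make the conflict larger.

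**2. Last entry date that allows 12 months** (end date minus 12 months).
- Against the S2 end: December 2022 − 12 months = December 2021.
- Against the study end: June 2023 − 12 months = June 2022.

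A participant enrolled in December 2022 has no follow-up by the S2 end and about 6 months by the study end. If follow-up runs to June 2023, everyone enrolled by December 2022 can still give 3- and 6-month data. This step needs no accrual assumption.

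**3. Number affected if the target is met.** Assumptions: the 98 recruited at submission is also the count at December 2021, the date Design gives as the present, and entry is even over the 12 months of 2022.

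| | Target 200 | Target 250 |
|---|---|---|
| Still to recruit in 2022 | 200 − 98 = 102 | 250 − 98 = 152 |
| Needed per month | 102/12 = 8.5 | 152/12 = 12.7 |
| No 12-month visit by December 2022 | 102 (51%) | 152 (61%) |
| No 12-month visit by June 2023 (second half of 2022) | 51 (25.5%) | 76 (30.4%) |

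**4. Evaluable at 12 months after 20% loss** (the loss rate in Sampling method).
- Everyone followed for 12 months: 200 × 0.8 = 160; 250 × 0.8 = 200.
- Follow-up to June 2023: (98 + 51) × 0.8 = 119; (98 + 76) × 0.8 = 139.
- Follow-up to December 2022: 98 × 0.8 = 78.

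**5. Sensitivity to accrual.**
- At the pandemic pace in the fieldwork section (2 to 3 per month), 24 to 36 enter in 2022, 12 to 18 of them after June. The total at the end of 2022 is then only 122 to 134.
- The average to date, counting November 2019 to December 2021, is 98/26 = 3.8 per month. At that pace the remaining 102 take 102/3.77 = 27 months, which runs past June 2023.
- The upper pre-lockdown pace (2 per week, 104/12 = 8.7 per month) gives 98 + 104 = 202, just reaching 200 by the end of 2022.

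Slower entry therefore lowers the number affected within 2022. If recruitment still continues until the target is reached, the last 12-month visit moves later.

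**The case against.** The strongest reply is that the end dates are forecasts and not data cut-offs. The article says it foresees June 2023 and expects recruitment by the end of 2022. Its Statistical analysis section places the calculation of rates after recruitment and follow-up are complete, and no text says that follow-up will be cut short. This stands. A reader might infer that the 12-month data are missing by design. The documents support only that the stated dates do not accommodate them, in a study that has already extended itself once.

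A reader might also infer that the abstinence rate will be biased downwards because late entrants will be counted as lost or as smokers. The article contains no such rule. Handling of missing data belongs to documents not shown, so that inference should not be drawn.

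Nor does the article name 12 months as the primary time point. Abstinence is assessed at 3, 6 and 12 months, and the sample size is framed in ex-smokers per 100 patient-years, to which partial follow-up can contribute. The counts in steps 3 and 4 depend on even entry and on the date of the 98, neither of which the article states. The figure of 78 takes the strictest reading of the S2 end.

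The month-label mismatches look clerical. Labels 40 and 44 agree with an eight-month extension, which suggests that the calendar dates were updated and the labels were not.

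One defence fails. Reading the end of 2022 as the end of fieldwork does not fit the sentence, which attaches that date to reaching the recruitment number.

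**Conclusion.** The stated dates contradict each other and should be reconciled. Against the S2 end, the last entry that allows a 12-month assessment is December 2021; against the study end it is June 2022. These two cut-offs follow from the article's dates alone.

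The size is conditional. If the target is met with even entry through 2022 from 98 in December 2021, about 51 to 76 participants (roughly 25 to 30%) have no 12-month assessment by June 2023, and 102 to 152 (51 to 61%) have none if S2 closes as dated. With 20% loss, about 119 to 139, or about 78, are evaluable instead of 160 to 200.

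The point established is a conflict in the schedule and an unstated, probably smaller, 12-month N. Bias in the abstinence rate is not established. The month-number errors are a secondary correction.

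**What to change.** Set one calendar for S2, S3 and the study end, then choose one of two routes.

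1. **Fix the last entry date for the 12-month analysis.** If follow-up runs to June 2023, state June 2022 as that date and extend the S2 follow-up window to June 2023, alongside S3. Treat later entrants as administratively censored at 12 months: they contribute 3- and 6-month data and are counted neither as lost nor as smokers. Restate the expected 12-month N (about 119 to 139 under the assumptions above). Beyond follow-up contacts up to the study end already foreseen, the cost is wording and a smaller stated N.
2. **Extend follow-up.** Date S2 follow-up to 12 months after the last enrolment, which is December 2023 if enrolment closes in December 2022. That is 12 months beyond the stated S2 end and 6 beyond the stated study end. The cost is larger than telephone calls alone, because reported abstinence must be verified by exhaled CO and Table 1 lists CO at 12 months.

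Under either route, correct the month numbers (40 and 44 for S2 and S3, 35 for December 2021) and give one length for the extension.

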#### Variables

Dependent variables include tobacco use, cannabis use, and alcohol use. Tobacco use is rated yes/no. If answering “yes”, we ask the about the tobacco consumption pattern, including nicotine dependence using the 6-item Fagerstrom test [35], and the type of tobacco or other products consumed (i.e., cigarettes, roll-your-own tobacco, combination of both, cigars, e-cigarettes, iQOS); smoking history, including the age when the participant starting smoking, maximum abstinence time, previous quit attempts, and resources used (i.e., none, self-help, professional support, pharmacological treatment, etc.); motivation to quit smoking, measured by a Likert scale from 0 to 10; and willingness to quit smoking, assessed by a 4-item questionnaire that, according to Prochaska and DiClemente’s model, classifies smokers into five stages: pre-contemplative, contemplative, preparation, action, and maintenance [36].

Cannabis use is rated yes/no. If “yes”, we recorded users pattern of consumption, problematic use (yes/no) [37], withdrawal symptoms identified using the Marijuana Craving Questionnaire [38] and reasons for use [39]. Alcohol use is rated yes/no and described according to the variables of consumption included in the Alcohol Use Disorders Identification Test (AUDIT) [40, 41]. A fourth dependent variable is participants’ self-reported smoking knowledge, attitude, and services (S-KAS) received during their treatment in SUD programs [42].

The primary outcome is abstinence from smoking (yes/no), which is self-reported and verified by the exhaled CO concentration only if they report to be abstinent. Self-reported abstinence is defined as “no smoking in the 7 days prior to the assessment point.” Seven-day abstinence was chosen as the consumption measure based on the consensus recommendation in practice guidelines for the assessment of abstinence in patients who are not motivated to quit smoking and who may remain abstinent during various periods of the study [43]. Number of quit attempts in the last year of  > 24-h duration [44] were also recorded. All dependent variables are assessed at baseline and 3, 6, and 12 months of follow-up (Table 1).

**Table 1 Tab1:** Study variables and collection time points (at baseline and follow-up)

Variables	Follow-up							
	Baseline	1 week	3 months		6 months		12 months	
			Abstinent	Not abstinent	Abstinent	Not abstinent	Abstinent	Not abstinent

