## Background

Tobacco use is the single most preventable morbidity and mortality [1]. Though progress has been made in reducing the prevalence of tobacco consumption in the general population [2], high prevalence (75.2% to 85.1%) remains in some vulnerable populations, particularly among people with substance use disorders (SUDs) [3]. Tobacco is responsible for 53% of the deaths in this group, reducing their life expectancy up to 25 years compared to the general population [4].

Smokers with SUDs take up smoking at an early age, consume more cigarettes per day (CPD), and frequently use different tobacco products [3], resulting in increased nicotine dependence [5] and a two to five times lower likelihood of cessation [6]. In SUD treatment settings, tobacco use has been historically considered a minor problem compared to other substances. Smoking was even once considered therapeutic in preventing substance use relapse [7]. People in treatment for SUDs have shown interest in quitting smoking [8] and make more serious attempts (abstinence  ≥ 24 h) when they are offered both psychological and pharmacological assistance [9].

Approximately 81,000 people annually are admitted to specialized treatment centers in Spain for outpatient treatment for SUDs [10]. Alcohol is responsible for four out of 10 admissions, and cannabis for two out of 10. Data from the Spanish Drug Observatory indicate that 44.7% of people admitted to outpatient treatment for alcohol and 83.3% admitted for cannabis use disorder have used tobacco in the previous 30 days [11]. However, only 44% of the SUD Programs in Catalonia (Spain) provide tobacco cessation treatment as part of their portfolios [12].

Given the high concomitant use of tobacco in patients in SUD treatment, its consequences to physical and mental health, and the low deployment of interventions in Spain, there is an urgent need to study which factors promote the introduction of smoking cessation in these programs.

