### Cohort of smokers

#### Participants

Inclusion criteria are (1) being a tobacco user (at least one cigarette per week), (2) initiating treatment for alcohol and/or cannabis in one of the SUD participating program, (3) age  ≥ 18 years, (4) under follow-up by participating clinicians, and (5) providing consent. Exclusion criteria are (1) inability to guarantee a 12-month follow-up (due to anticipated mobility problems, etc.) and (2) severe cognitive impairment and/or other communication problems (i.e., not speaking Spanish or Catalan).

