#### Sampling method

The incidence of unassisted smoking cessation is seven ex-smokers per 100 patient-years [33]. We estimate that, among this sample, being in contact with the health system may increase this rate to 10 ex-smokers per 100 patient-years (i.e., a relative risk [RR] of quitting smoking of 2.0). Therefore, to detect this RR assuming an alpha error of 5%, a beta error  < 20%, and losses of 20%, we require 366 participants. The sample size was calculated using the GRANMO program [34]. This sample size is achievable in one year as the 48 centers in the province of Barcelona treat approximately 5000 new cases for alcohol and 1500 new cases for cannabis yearly (target population: 6,500 participants) [12]. On average, the 10–12 selected study centers should treat approximately 1,625 people/year. Smokers in treatment for alcohol and/or cannabis use are being recruited consecutively for one year.

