**Cannabis**								
Consumption once in lifetime	X		X		X		X	
Consumption in the last month	X		X	X	X	X	X	X
Frequency of cannabis use in the last month	X			X		X		X
Problem cannabis use (only for patients under treatment for alcohol abuse)	X		X	X	X	X	X	X
Frequency of use, consumption, and interaction with tobacco in the last 30 days	X		X	X	X	X	X	X
Context of cannabis smoking	X			X		X		X
Latest consumption	X		X	X	X	X	X	X
Age at start of consumption	X							
Reasons for cannabis use	X							
Previous attempts to stop using cannabis	X							
Maximum withdrawal time	X							
Resources used to stop using cannabis	X							
Willingness to quit cannabis use	X		X	X	X	X	X	X
Motivation to quit cannabis use	X			X		X		X
Efficacy	X		X	X	X	X	X	X
Environment	X							

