**Primary outcome**								
Breathed CO concentration	X		X	X	X	X	X	X

Independent variables include sociodemographic data (sex, age, employment status and occupation, and education level), self-perceived state of health addressed by the question “How would you say your general health is?”, measures of mental and physical health according to the DSM-V [45], quality of life according to the General Health Questionnaire (GHQ-12) [46], and level of previous smoking cessation treatment received using questions about standard interventions included in the Smoking Cessation Guidelines (i.e., advice, reduction recommendation, educational material, cognitive-behavioral treatment, pharmacological treatment, nothing) [47].

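### Exhaled CO cannot tell tobacco smoke from cannabis smoke, so abstinence verified by CO alone could bias the abstinence RR for treatment substance

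*Protocol article*

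**What the plan says.** In the Protocol article, Variables (cohort of smokers), the primary outcome is abstinence from smoking, yes or no. It is self-reported and "verified by the exhaled CO concentration only if they report to be abstinent". Self-reported abstinence means "no smoking in the 7 days prior to the assessment point"; the definition does not add the word tobacco. Table 1 lists "Breathed CO concentration" as the entry under primary outcome at baseline and at 3, 6 and 12 months.

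The inclusion criteria admit tobacco users "initiating treatment for alcohol and/or cannabis in one of the SUD participating program". The Statistical analysis section fits a Poisson model with robust variance to abstinence and to quit attempts, with independent variables that include "the substance of treatment, sex, types of cessation support".

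The cannabis block of Table 1 records latest consumption and "Frequency of use, consumption, and interaction with tobacco in the last 30 days". Both rows are marked at 3, 6 and 12 months, in the abstinent and the not-abstinent columns. Nothing in the article connects these items to the reading of the CO result.

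**The concern.** Any burning plant material gives off CO, so a raised reading shows recent smoke exposure but not its source. In an ordinary tobacco cohort this matters little. Here, part of the cohort is in treatment for a substance that is commonly smoked, and cannabis use during follow-up is itself one of the study's dependent variables, so some continued use has to be expected.

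A check made only on reported abstainers can remove abstainers but never add any. If it wrongly removes people whose CO comes from cannabis, and these people sit mainly in the cannabis-treated group, the outcome is measured differently across levels of a model predictor. Part of an apparent finding that cannabis patients quit tobacco less often than alcohol patients could then come from the verifier. Aim 3 of the article is to identify predictors of smoking cessation, so this estimate matters to the study. Quit attempts are not CO-verified and are not affected.

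**Working it through.** The plan states no figure on this point, so there is nothing to reproduce. The calculation below only gives scale.

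**1. How large is the cannabis group?** Sampling method gives "approximately 5000 new cases for alcohol and 1500 new cases for cannabis yearly". Background gives "44.7% of people admitted to outpatient treatment for alcohol and 83.3% admitted for cannabis use disorder have used tobacco in the previous 30 days".

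- Tobacco users among cannabis admissions: 1500 × 0.833 = 1249.5
- Tobacco users among alcohol admissions: 5000 × 0.447 = 2235
- Cannabis share of tobacco users: 1249.5 / (1249.5 + 2235) = 35.9%

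If enrolment follows these shares, about 72 of 200 or 90 of 250 participants (the current recruitment target) would be cannabis patients.

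**2. Effect on the treatment-substance RR.** Let q be the share of true tobacco abstainers who fail verification because of cannabis smoke, and p the true abstinence, taken as equal in both groups.

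Observed RR (cannabis vs alcohol) = p(1 − q_can) / [p(1 − q_alc)] = (1 − q_can) / (1 − q_alc)

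The value of p cancels. The documents give no value for q, so the values below are assumptions.

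| q_can | RR if q_alc = 0 | RR if q_alc = 10% |
|---|---|---|
| 10% | 0.90 | 0.90/0.90 = 1.00 |
| 25% | 0.75 | 0.75/0.90 = 0.83 |
| 50% | 0.50 | 0.50/0.90 = 0.56 |

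The true RR is 1.00 throughout. The bias is downward for cannabis whenever q_can exceeds q_alc, and absent when they are equal.

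**3. How few people does this take?** Sampling method expects 10 ex-smokers per 100 patient-years. Read as 10% at 12 months, that is 72 × 0.10 ≈ 7 to 90 × 0.10 = 9 true abstainers in the cannabis group before losses. Two wrong removals would cut the observed count by 2/9 = 22% to 2/7.2 = 28%.

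**4. Effect on the RR for cessation support.** Within one treatment substance, let true abstinence be p1 with support and p0 without. If q is the same in both, the observed RR is p1(1 − q) / [p0(1 − q)] = p1/p0. The RR is unchanged; only events, and so precision, are lost.

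**The case against.** Several objections limit the point.

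- **Overruling is inferred.** A reader might infer that the plan lets a raised CO overrule self-report. It says only that abstinence is verified, and prints no cut-off and no rule for discordant results. A condensed article may leave both to the full protocol or analysis plan, so their absence is not the complaint. What stands is that the article itself names one verifier that is not specific to tobacco. A check that could never change a classification would not be verification.
- **The subgroup is narrow.** A reader might infer that CO misclassifies cannabis smokers in general. It does not. Someone who mixes cannabis with tobacco is not a tobacco abstainer, and there a raised CO corrects a false report. The error needs tobacco cessation plus recent smoking of cannabis without tobacco. The Discussion recognises cannabis used alone as well as combined with tobacco, but the documents give no frequency.
- **The groups overlap.** Table 1 follows problem cannabis use in alcohol patients, and participants may be treated for both substances. Setting q_alc to zero is therefore an extreme case, which is why the second column is shown.
- **CO may seldom be available.** Follow-up moved to telephone in March 2020, and no way of obtaining CO by telephone is described. Less CO data means less reach for this problem.
- **Smoking might include cannabis.** On that reading a cannabis-derived CO rise is no error. But Table 1 places abstinence in its tobacco block and the aims concern tobacco, so the tobacco reading is the natural one. On the other reading, the outcome would itself partly measure stopping cannabis, and the treatment-substance RR would be harder still to interpret.
- **Support is not shown to be affected.** A reader might infer that the association with cessation support is diluted. Step 4 of the working shows that this does not follow, and nothing in the documents suggests that q differs by support.

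**Conclusion.** The point holds in a limited form. CO is the only stated verifier, it cannot separate tobacco from cannabis smoke, and treatment substance is a model predictor of the verified outcome. True tobacco abstainers could therefore be removed unevenly, probably more often in the cannabis-treated group, which would bias that group's abstinence RR downward.

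The documents do not support any single figure for the bias. Under the assumed q_can of 10-50%, a true RR of 1.00 would be observed as 0.90 to 0.50 with q_alc = 0, and as 1.00 to 0.56 with q_alc = 10%. This rests on failed verification counting as not abstinent, on equal true abstinence in the two groups, and on a CO reading having been obtained. The RR for cessation support is unbiased unless q differs by support. This is a cheap improvement to the outcome definition and its reporting, not a fault that undermines the design.

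**What to change.** 1. State that the primary outcome is tobacco abstinence, and that cannabis mixed with tobacco counts as tobacco smoking, identified from the interaction item. That item covers 30 days and the outcome covers 7, so say how mixed use earlier in the 30 days is treated.
2. Flag each participant who reports tobacco abstinence, has a raised CO, and reports recent cannabis use without tobacco (from the latest-consumption item).
3. Report abstinence by treatment substance, and the treatment-substance RR, under two classifications: CO-verified for everyone, and self-report for the flagged cases. Give the number flagged in each group.

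If the two results agree, the issue closes. If they differ, the gap shows how far the estimate depends on the verifier.

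The cost is a few sentences and one sensitivity analysis on variables already collected at 3, 6 and 12 months. The downside is that flagged cases stay unverified under the second classification. Because they are likely to be mostly cannabis patients, that classification carries its own uneven error if some of them are undisclosed tobacco smokers. Both results should therefore be shown together.
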